##### Grafting

With the inclusion of deep dermal partial-thickness and full-thickness burns in the eligibility criteria, it is anticipated that some participants will ultimately require skin grafting to achieve wound closure. All surgical procedures will be documented by investigators, but data collection will be discontinued for these patients at the point of grafting. Any data obtained prior to grafting will be included in the final analysis following an intention-to-treat methodology.

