## Methods/design

### Hypothesis and objectives

The central aim of this trial is to investigate the efficacy of NPWT as an adjunct to standard therapy in the treatment of paediatric burns. The research will measure the effects of NPWT on time to re-epithelialisation, pain and burn wound progression, and determine whether it produces outcomes superior to those of standard therapy alone. Based on data from a pilot study, it is hypothesised that NPWT will accelerate healing and reduce levels of pain and pruritus between dressing changes. Removal and re-application of the NPWT system is not expected to cause significantly more pain than standard dressing changes. In terms of the impacts on overall costs, it is suspected that NPWT may increase resource usage and costs in the acute phase of treatment, but, by virtue of faster re-epithelialisation and reduced scar formation, curb the personnel and material costs required for long-term scar management.

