##### Scar and skin assessments

At 3 and 6 months following the burn injury, face-to-face follow-ups will be completed with all participants to conduct skin or scar reviews in conjunction with occupational therapy.

Ultrasound will be used to measure the thickness of the healed wound or scar. Scans will be taken centrally at each site of interest with the BT12 Venue 40 MSK ultrasound machine (General Electric, Little Chalfont, UK). The investigators will record and calculate an average of three thickness measurements within the central area at the time of the scan. These measurements will be compared to those taken from scans of healthy unburned skin contralateral to the site of the burn. Digital copies of the scans will be saved for later evaluations by blinded reviewers.

An objective quantification of the lightness, erythema, and pigmentation of the healed wound or scar will be obtained using the DSM II ColorMeter (Cortex Technology, Hadsund, Denmark). In paediatric studies, the device has exhibited high levels of inter-rater reliability [116], including among children with burn scars [117]. At each follow-up, two measurements will be taken of both the site of interest and a region of healthy skin for comparison.

The Patient and Observer Scar Assessment Scale (POSAS) will also be completed with the child (if over the age of 8 years) and caregiver. As a scar severity evaluation tool, the POSAS is both reliable and feasible [118–120], with an observer scale that shows adequate reliability in the assessment of scar appearance in children [117]. Another instrument, the Brisbane Burn Scar Impact Profile (BBSIP), will be used to measure scar patients’ physical and sensory symptoms as well as their health-related quality of life. Developed primarily for children, the BBSIP has undergone preliminary validation in paediatric patients at the participating burns centre [121].

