##### Resource use and costs

Resource usage (and costs) for the care of each patient will be recorded from the perspective of the health service consistent with prior studies in the field [122, 123]. This will include details of the trial interventions, including the number of clinical visits, the duration of each visit, the dosages of analgesic medications prescribed, the quantity of dressings and NPWT products used, and associated labour time. Resource use will be costed at market rates (e.g., clinician time attributable to each participant will be costed based on relevant state-award salary rates). For patients requiring subsequent scar management, details of scar management (including scar interventions and associated clinician labour time) will also be recorded for each patient for the duration of the trial.

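### Data collection stops at grafting, contradicting the scar review promised to all participants and the costs promised for each patient: scar outcomes become ungrafted-only and post-graft costs are truncated

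*Protocol article*

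**What the plan says.** Four parts of the protocol article bear on this.

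- **Grafting.** Deep dermal partial-thickness and full-thickness burns are eligible, and "it is anticipated that some participants will ultimately require skin grafting to achieve wound closure". On what is then recorded: "All surgical procedures will be documented by investigators", but "data collection will be discontinued for these patients at the point of grafting". On analysis: "Any data obtained prior to grafting will be included in the final analysis following an intention-to-treat methodology".
- **Scar and skin assessments.** At 3 and 6 months after injury, "face-to-face follow-ups will be completed with all participants to conduct skin or scar reviews in conjunction with occupational therapy". The measures are ultrasound thickness, colour, POSAS and BBSIP. Grafted children are not excepted.
- **Resource use and costs.** "Resource usage (and costs) for the care of each patient will be recorded from the perspective of the health service". Where a child needs scar management, its details are to be recorded throughout the trial. Again there is no exception for grafted children.
- **Hypothesis and objectives.** NPWT may cost more in the acute phase but, through faster healing and less scarring, "curb the personnel and material costs required for long-term scar management".

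**The concern.** The stop in the Grafting section carries no limit to acute-phase measures, and the sentence after it confines the analysis to data obtained before the graft. Taken literally, it cancels the 3- and 6-month reviews and the later cost recording for a group the protocol expects to exist.

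For the scar outcomes this is a selection made after randomisation. The Background says that deeper burns are associated with significant scarring and are almost always debrided and grafted, so the children removed are likely to be at higher scar risk. NPWT is being tested for faster healing and less wound progression, so it could plausibly alter who is grafted. A scar comparison among the ungrafted is then not protected by randomisation.

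For costs the problem is different. Grafted children stay in the comparison, but what they cost after grafting is unrecorded except for the documented surgery. The hypothesis about long-term scar-management costs depends partly on those later costs.

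**Working it through.** **1. Can the sections be reconciled as they stand?** Scar reviews cover all participants, and costs cover each patient. The Grafting section ends collection for some of those same children before either endpoint is complete. No sentence ranks one section above the others. Elsewhere the protocol takes the opposite line: under Adverse events, a child who has an adverse event or is switched to another dressing stays under intention-to-treat data collection. Grafting is the exception.

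**2. Would imputation repair it?** Data analysis allows multiple imputation where suitable. Under the Grafting rule no grafted child has a 3- or 6-month scar value, so there would be no observed post-graft scar data to inform the imputation. An analysis plan cannot recover measurements that were never taken.

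**3. Number of children affected.** The documents give no graft rate. Assuming 2% to 10% in each arm of 52, the loss from 104 children is 104 × 0.02 ≈ 2 to 104 × 0.10 ≈ 10.

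**4. Scar outcomes (illustration, all inputs assumed).** Let ungrafted children have the same mean in both arms and let grafted children scar D standard deviations (SD) worse. With graft proportions gC (control) and gT (NPWT), the difference in all randomised children is (gT − gC) × D, while the ungrafted comparison shows 0.

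- gC = 10%, gT = 5%: (0.05 − 0.10) × 1 = −0.05 SD; with D = 2, −0.10 SD.
- gC = 5%, gT = 10%: +0.05 to +0.10 SD, the reverse direction.
- Equal rates: 0.

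This leaves out a second route. If NPWT spared some deep burns from grafting, those children would enter the NPWT side of the ungrafted comparison and worsen its mean.

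**5. Costs (illustration, all inputs assumed).** Set an ungrafted course at 1 unit and a graft episode at k units. Mean cost per arm is (1 − p) × 1 + p × k, where p is the graft proportion. The relative saving is 1 − (NPWT mean ÷ control mean). NPWT device cost is left out throughout.

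| Graft rate, control v NPWT | k | Control mean | NPWT mean | Saving |
|---|---|---|---|---|
| 9% v 4.5% | 10 | 0.91 + 0.90 = 1.81 | 0.955 + 0.45 = 1.405 | 22% |
| 9% v 4.5% | 5 | 0.91 + 0.45 = 1.36 | 0.955 + 0.225 = 1.18 | 13% |
| 2% v 1% | 10 | 0.98 + 0.20 = 1.18 | 0.99 + 0.10 = 1.09 | 8% |
| 2% v 1% | 5 | 0.98 + 0.10 = 1.08 | 0.99 + 0.05 = 1.04 | 4% |
| equal rates | any | equal | equal | 0% |

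If every post-graft cost is lost and pre-graft cost is about 1 unit, both arms average about 1.0 and the whole saving is hidden. If the documented surgery is costed and makes up a fraction f of the extra cost (k − 1), the share f of the difference is recovered and only 1 − f is hidden. If NPWT raised the graft rate, the hidden quantity would be an extra cost.

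**6. Primary sample size.** A two-sample t-test with difference 3.4 days, SD 5.4, two-sided 0.05 and 80% power needs 40.58, so 41 per arm. Then 41 ÷ 0.80 = 51.25, so 52 per arm and 104 in total, as stated. This point does not change it.

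**The case against.** The strongest reply is that the consequences are limited, and much of it stands.

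- **Grafted children do not leave the cost comparison.** A reader might infer that they do, and that randomisation is broken there too. The Grafting section keeps their pre-graft data in the analysis and has surgery documented. The cost defect is truncation; the selection argument applies only to the 3- and 6-month scar outcomes.
- **The worst scars and the largest costs are not shown to be lost.** The Background ties depth to scarring and to grafting, but does not say that grafted sites end with the worst scars. Nothing compares the costs of grafted and ungrafted children.
- **The cost hypothesis can still be addressed in part.** It might seem unanswerable, but scar management is still recorded for children who heal without a graft.
- **Graft rates may be low.** Eligible burns cover under 5% of body surface, and the Background reports that 87-93% of paediatric burns are treated wholly as outpatients. Even 9% v 4.5% of 52 is only about 5 v 2 children, and 22% is the top of an assumed range.
- **No hypothesis about grafting is stated.** That NPWT affects it is an inference from the aims on healing and wound progression.

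One could also argue that the stop was meant for acute measures only. The text does not say so, and the sentence on pre-graft data points the other way. None of these replies removes the contradiction or restores the missing scar data.

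**Conclusion.** The contradiction is explicit and should be resolved. Followed as written, the 3- and 6-month scar comparison excludes grafted children, a post-randomisation subset linked to burn depth and scar risk. Cost data for those children are truncated at grafting, so the question about long-term scar-management costs is answered incompletely and possibly with bias.

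The size cannot be fixed from the documents. Under the assumptions shown, the scar effect is modest: 0.05 to 0.10 SD hidden at 10% v 5% grafted. The hidden cost saving runs from 0% at equal graft rates, through 4-8% at 2% v 1%, to 13-22% at 9% v 4.5%. These cost figures assume that all post-graft cost is lost, and they shrink if documented surgery is costed. Only secondary outcomes are involved. The documents do not support a claim that the cost comparison is confined to ungrafted children or that the cost hypothesis is beyond answer.

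**What to change.** Amend the Grafting section so that it agrees with the sections on scar assessment and resource use. For example: *Healing assessments and dressing-change measures end at grafting. Adverse-event and resource-use recording, and the 3- and 6-month scar, POSAS and BBSIP reviews, continue for all randomised participants.* State that documented surgery is costed and that these outcomes are analysed in all randomised children.

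This version is dated 15 January 2019 and recruitment began on 2 May 2018, with 103 children enrolled. Children injured after about mid-July 2018 therefore still had their 6-month review ahead. Where a review date has passed, retrieve resource use from hospital records and report the missed scar measurements as missing, since those records may not hold ultrasound, colour, POSAS or BBSIP values.

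The cost is a short amendment and a few extra follow-up records. The change concerns data collection only and leaves clinical care and the primary sample size as they are.

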##### Adverse events

If a patient experiences an adverse event such as an infection or allergic reaction during the trial, investigators will record the event (even if not directly related to the child’s burn) and document any changes made to the child’s clinical care to address the issue. Should a consultant conclude that a particular dressing is not appropriate for a participant’s care, even in the absence of an adverse event, they will be free to select an alternative dressing. In both scenarios, data collection and analysis will adhere to intention-to-treat principles.

##### Wound exudate collection and analysis

Wound exudate has been increasingly recognised as a potentially rich source of information about the burn wound microenvironment [1]. Theoretically, NPWT is the ideal instrument for collecting this fluid. It extracts exudate directly from the interstitium and stores it in disposable canisters. Practically, however, the NPWT canisters have been engineered, for safety, to preclude any direct access to the collected exudate.

To obtain this fluid, therefore, investigators will inspect the used suction tube connected to the canister at every dressing change after the NPWT apparatus is replaced. If there is any visible wound aspirate, the tubing will be punctured so that the fluid can be drained into collection tubes. At the end of the clinical visit, the samples will be centrifuged at 855× relative centrifugal force for 5 minutes and frozen in aliquots at −80°C.

Once all the samples have been collected, they will be processed for SWATH™ mass spectrometry analysis, using techniques described previously [124]. Briefly, a 60-μg aliquot of each sample will be digested by trypsin, desalted, concentrated, and analysed using liquid chromatography-tandem mass spectrometry (LC-MS/MS) in data-independent acquisition mode for peptide identification and SWATH™ acquisition mode for peptide abundance. An existing peptide spectral ion library [125] will be used to identify the peptide products and generate proteomic profiles of the microenvironments of the different wounds. These profiles will be compared against one another as well as the proteomic profiles of paediatric burn blister fluid described previously by Zang et al. [125, 126]

The remainder of the samples will be subjected to more targeted assays to assess their levels of specific cytokines and other factors involved in the processes of burn wound conversion and healing. Enzyme-linked immunosorbent assay (ELISA) will be employed to detect markers of neovascularisation, re-epithelialisation and inflammation (e.g., VEGF, FGF-2, EGF, IL-8 and TNF-α). If sufficient quantities of exudate are collected, the assays will help to determine how these factors vary with time, depth and burn aetiology.

#### Sample size

The sample size was derived from the primary endpoint, time to re-epithelialisation. Previous burns research has reported a mean healing time with standard Acticoat™ therapy of 12.4 days (SD = 5.4) [127]. In light of findings by Deitch et al*.* [29] and Cubison et al*.* [30] that showed healing times under 10 days post-burn were associated with no hypertrophic scarring, the investigators considered that a 3.4-day reduction in time to re-epithelialisation would likely represent a clinically meaningful difference. Therefore, the study will aim to recruit a minimum of 104 participants for >80% power (assuming up to 20% drop-out and a significance level of 0.05). In 2017, approximately 1100 patients presented to the OPD for burns treatment. Of these, more than 90% satisfied the inclusion criteria of the present study. Therefore, it is expected that recruitment will be completed within a span of 9 months.

#### Data collection and management

Investigators will input data directly into the REDCap application via an electronic tablet. The application is hosted on a secure firewall-protected server at the research institute affiliated with the burns clinical unit. REDCap generates an audit trail that tracks all user activity, including data entry, manipulation and exportation. Any data exported for statistical analysis will be stored on a password-protected computer within the research institute. Access to passwords and codes will be limited to investigators involved in the trial. If any researcher leaves the project, all passwords will be replaced.

#### Data analysis

Conventional descriptive statistics will be used to describe the characteristics of the sample.

The potential effect of time to treatment, burn depth, burn TBSA, mechanism of injury, anatomical location of the burn and skin type will also be tested against primary and secondary measures in univariate analyses. Variables with *p*
< 0.1 will be included as covariates in the primary and secondary analyses. Sensitivity analyses will also be conducted without adjustment for covariates.

Generalised linear (mixed) models will be prepared to examine primary and secondary outcomes across time and between groups, with patients as random effect where analyses include repeated measures within a patient. If mixed models do not converge with patient as a random effect, robust variance estimates for cluster-correlated data will be used [128]. For outcomes with repeated measures, the fixed effects of time, group and interaction time by group will be tested. Data will be analysed as intention-to-treat (primary analysis) and on a per protocol basis (sensitivity analysis) if deviations from the protocol occur. Missing data will be handled using multiple imputation where appropriate. Significance will be set at 0.05. Statistical analyses will be performed using Stata (StataCorp LLC College Station, TX:) or SPSS (IBM Corp, Armonk, NY, USA).

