#### Participants

##### Eligibility criteria

All paediatric burns patients presenting to the hospital’s emergency department (ED) or burns OPD will be considered for eligibility. Children will satisfy the inclusion criteria if they are under 17 years of age, possess a thermal burn covering <5% of their TBSA and present within 7 days of their injury. Exclusion criteria include burns that are located on the face or deemed by clinicians to be trivial in nature (i.e., not in need of further treatment). The eligibility criteria are listed in Table 1.

**Table 1 Tab1:** Eligibility criteria

Inclusion criteria	Exclusion criteria
0–16 years of age TBSA < 5% Thermal burns Presentation to ED or burns OPD within 7 days of injury	Facial burns Trivial burns

*TBSA* total body surface area, *ED* emergency department, *OPD* outpatient department

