#### Primary outcome measure

##### Time to re-epithelialisation

The primary outcome will be time to full re-epithelialisation, as measured by the number of days from the injury to 95% re-epithelialisation of the burn wound. Percentage re-epithelialisation will be assessed at every clinical visit using multiple methods. A treating consultant will first perform an examination and record their assessment. Digital 3D photographs will then be taken of the burn using the 3DLife Viz II (Quantificare, Valbonne, France) and the D400 3D (Intel, Santa Clara, US) cameras. These photographs will be analysed using the software programs DermaPix (Quantificare, Valbonne, France) and 3D WoundCare (GPC, Swansea, UK), respectively, and undergo blinded review by a panel of three burns clinicians.

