Any attempts to extrapolate findings from the existing adult studies to a paediatric setting must be met with caution, not only due to the small sample sizes and methodological limitations of these trials, but also because young children differ markedly from adults in skin thickness and composition [132, 133], body surface area [134], and formation rates of granulation tissue [135]. The reluctance to employ NPWT in paediatric populations appears to stem from concerns about possible side effects, including bleeding, ischaemia and elevated pain [93]. However, reports of adverse events are rare in the literature, and the technique is widely regarded as safe when applied and monitored as per device instructions [136]. NPWT is known to cause pain at pressures greater than 125 mmHg [137], but this is well above the standard range preferred by the participating hospital. Anecdotally, the highest levels of pain experienced by paediatric patients undergoing NPWT are reported during removal of the adhesive film required to maintain the airtight seal. It is anticipated that with the application of Niltac™ prior to extraction, removing and re-applying the NPWT system will be no more painful than regular dressing changes. The overall risks of NPWT are, therefore, minimal, with most research focusing on the use of the therapy in children indicating that it is especially suited for paediatrics, as it reduces the frequency of procedures and allows for greater mobility than some standard dressings [138].

The trial was deliberately designed to serve as a pragmatic study of the efficacy of NPWT in the treatment of the broad spectrum of thermal burn injuries that routinely present to the participating ED and OPD. Especially for the latter, the burns seen over the course of even a single day tend to vary significantly in terms of first aid, prior treatment and time to presentation. For this reason, investigators have set a sample size that is large enough to account for the wide variability and allow for a statistical comparison of different groups.

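### The primary model's covariates are chosen by a univariate p<0.1 screen on the trial's own outcomes, so the adjusted primary estimate is not fixed in advance and adjustment for time from injury, burn depth and age stratum is not guaranteed

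*Protocol article*

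**What the plan says.** The covariate rule is in the protocol article, section Data analysis. "The potential effect of time to treatment, burn depth, burn TBSA, mechanism of injury, anatomical location of the burn and skin type" are the factors that "will also be tested against primary and secondary measures in univariate analyses". Those with p below 0.1 "will be included as covariates in the primary and secondary analyses". No factor is forced in. The analysis without covariates is named only as a sensitivity analysis, so the screened model is the primary one.

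Three other parts of the article bear on this rule:

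- Time to re-epithelialisation: the endpoint is "the number of days from the injury to 95% re-epithelialisation of the burn wound".
- Eligibility criteria: children qualify if they "present within 7 days of their injury". The Discussion adds that the burns seen "tend to vary significantly in terms of first aid, prior treatment and time to presentation".
- Randomisation: allocation is stratified by age in three groups (0 to 3, 4 to 7 and 8 to 16 years). Age is not among the six screened factors.

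The Background section describes healing time as closely linked to burn depth.

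**The concern.** A primary analysis should be one model that can be written down before outcomes are seen. Here the list and the threshold are fixed, but the model that results is not. It depends on six significance tests in roughly 83 children (104 less 20%), and such tests keep or discard moderately prognostic factors largely by chance.

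Two factors should not be left to that. Depth is already regarded as prognostic in the protocol, so there is no need to ask the trial data whether it matters. Time to treatment is different in kind: the clock starts at injury, so the days before treatment are part of each child's endpoint value, and negative pressure therapy cannot shorten them. In addition, the model as described has no term for the factor used to stratify the randomisation.

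What is at stake is a settled primary estimate and some precision, not the validity of the comparison.

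**Working it through.** **Reproducing the plan's sample size.** Inputs from Sample size: SD 5.4 days, difference 3.4 days, alpha 0.05 (two-sided assumed), power above 80%, 20% drop-out. A two-sample t-test needs 41 per arm. Then 41/0.8 = 51.25, rounded up to 52 per arm, or 104, which matches the plan. With 42 per arm left (84 children), t-test power is 81.4%.

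**Number of possible primary models.** Six factors, each in or out: 2^6 = 64 covariate sets.

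**Chance that time to treatment is omitted.** The documents give no SD for it, so a range s is assumed. Assume also that it adds day for day to an endpoint with total SD 5.4. Then:

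- correlation r = s/5.4, and share of variance = s²/5.4²;
- noncentrality = r√n/√(1−r²), with the two-sided 0.1 critical value of t on n−2 degrees of freedom.

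Example, s = 1 and n = 84: r = 0.185; noncentrality = 0.185 × 9.165/0.983 = 1.73; probability of p<0.1 = 0.527; probability of omission = 47%.

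| Assumed SD (days) | Share of variance | Omitted, n = 84 | Omitted, n = 104 |
|---|---|---|---|
| 0.5 | 0.9% | 78% | 75% |
| 0.75 | 1.9% | 64% | 59% |
| 1 | 3.4% | 47% | 40% |
| 1.5 | 7.7% | 16% | 10% |
| 2 | 13.7% | 2% | 1% |

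**Simulating the whole rule, first setting.** 84 children, 8,000 replicates per scenario. Assumed effects: time to treatment day for day, with a skewed distribution of SD about 1 or 1.5 days capped at 7; deep burn in 25% of children, adding 4 days; burn area 0.8 day per SD; mechanism 1 day, location 0.5 day, skin type none. Total SD 5.4.

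| | Screen | All six fixed | Unadjusted |
|---|---|---|---|
| Type I error, SD 1 / 1.5 | 5.2% / 5.0% | 5.1% / 5.0% | 5.0% / 5.0% |
| Power, SD 1 / 1.5 | 84.7% / 86.5% | 85.1% / 87.1% | 81.9% / 81.3% |

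Depth was dropped in 8 to 11% of trials and burn area in 61 to 64%. Of the 64 sets, 59 to 61 occurred. At a true 3.4-day effect, the screened and unadjusted models disagreed on significance at 0.05 in 9 to 10% of trials. That figure compares screened with unadjusted, not screened with fixed; it shows only that the choice of covariates can change the conclusion.

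**Second setting, stronger assumed prognosis.** One factor with r = 0.5 and five with r = 0.15 to 0.25: power was 95.9% with all six fixed, 93.9% with the screen and 81.5% unadjusted; type I error was 4.9%. A factor with r = 0.2 passed the screen 54 to 58% of the time, and one with r = 0.15 passed 36 to 39%. Further runs put the advantage of six fixed factors over the screen at about 1 to 3 points.

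**The four-variable set** (time from injury, depth, burn area, age stratum, with age assumed unrelated to healing; 5,000 replicates):

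| Assumed correlations | Screen | Four variables |
|---|---|---|
| Depth 0.5, other five factors 0.2 | 93.6% | 92.4% |
| Time 0.2, depth 0.5, area 0.15, other three 0.25 | 95.4% | 91.0% |
| Time 0.25, depth 0.4, others 0.1 | 88.4% | 88.7% |

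Further runs with other assumed values ranged from 4 points worse than the screen (91.4% against 95.4%) to 2 points better (91.6% against 89.7%).

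**The case against.** The strongest defence is that the rule is fully mechanical. The candidates, the threshold, the consequence of passing and an unadjusted sensitivity analysis are all stated beforehand. No analyst chooses covariates by looking at the treatment effect. All of that stands.

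A reader might infer that the screen inflates the false-positive rate, or that leaving out time from injury biases the comparison. Neither is supported. Simulated type I error stays at about 5%, and under randomisation the pre-treatment days are balanced in expectation, so omitting them adds noise rather than bias. The omission is also partly self-limiting: the table shows it is likely when the variance share is small and rare when it is large.

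A reader might also infer that any fixed set is more powerful than the screen. That holds only modestly for all six factors, and it can reverse for a shorter set if the factors left out are strongly prognostic. The large contrast, with the unadjusted model, is beside the point because the plan does not use that model as primary.

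Different covariates for different outcomes are not in themselves an error.

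What the defence does not answer is that the primary estimate still depends on which of 64 models the data select, that two factors with a clear claim to inclusion are not guaranteed a place, and that the stratifier is not in the list. An unseen analysis plan does not settle this, because the screen is a rule the article states.

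**Conclusion.** The point holds as a weakness in how the primary estimate is specified. It is not a threat to validity. Against fixing all six listed factors, the cost is about 0 to 3 power points, and every adjusted model examined stays above the planned 80%. The risk of omitting time to treatment runs from 78% (SD 0.5 day) to 2% (SD 2 days) with 84 children.

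These sizes rest on assumed covariate effects, correlations and an assumed spread of time to treatment, none of which the documents give. The conclusion that the model is not fixed rests on the text alone. The change is worth making because it is nearly free.

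**What to change.** Remove the p<0.1 screen and prespecify one covariate set for the primary analysis, always including:

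- days from injury to randomisation;
- burn depth and burn area, both as assessed at baseline (Data analysis does not say which assessment is meant, and Wound depth and progression repeats laser Doppler imaging at the first follow-up, after treatment has begun);
- the age stratum.

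For mechanism, location and skin type, choose one of two courses before database lock: keep them fixed in the model with sparse categories collapsed in advance, or state that they are left out. Keep the unadjusted sensitivity analysis as planned.

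The sample size stays at 104, and the change is one of wording to factors already named in the plan. Trial status reports 103 children recruited, with 3- and 6-month follow-up in the design, so there was still time before lock. The cost is a few degrees of freedom and, if the last three factors are dropped and prove strongly prognostic, possibly slightly less precision. The justification should be a fixed primary estimate with guaranteed adjustment for the endpoint's pre-treatment component and for the stratifier.
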